## Abstract

**Background:**

HIV post-exposure prophylaxis (PEP) is an evidence-based biomedical HIV prevention strategy consisting of a 28-day course of highly active antiretroviral therapy after recent potential exposure to HIV. However, awareness and uptake of PEP among men who have sex with men (MSM) are very low. Innovative and effective methods are needed to support PEP implementation among MSM. This work reports a protocol to design and evaluate an online-to-offline-based delivery model for HIV PEP uptake (O2O-PEP) in Chinese MSM.

**Methods and analysis:**

This will be a two-phase study. In phase 1, we will develop an O2O-PEP model delivered through the WeChat mini-app (an app built into the WeChat platform). The O2O-PEP model initially includes four core components: a gamification-based education package for PEP, an online HIV risk assessment tool, a free online booking system for PEP initiation, and offline PEP prescription in the study hospitals. In phase 2, a two-arm pilot stratified randomized controlled trial comparing the O2O-PEP group with the standard care group will be designed to assess the feasibility, usability, and preliminary evidence of the efficacy of the O2O-PEP model in increasing PEP uptake among Chinese MSM. Model feasibility and usability will be further explored for broader model implementation.

**Discussion:**

The O2O-PEP model is one of the first interventions in China aiming to promote PEP initiation in Chinese MSM. Components in the O2O-PEP model could assist MSM in better understanding their HIV infection risk and increasing accessibility of PEP. Moreover, coupled with online and offline recruitment, the O2O-PEP model has great potential to reach and engage MSM who are not involved in care by traditional methods.

**Clinical trial registration:**

No. ChiCTR2200062538.

## Introduction

The HIV epidemic continues to be a major public health challenge among men who have sex with men (MSM) globally (1). Systematic reviews indicate an increasing HIV prevalence among MSM in China from 1.4% in 2001 to 8% in 2015 (2, 3). In larger, urban areas of China, MSM has been found to account for more than 50% of all newly diagnosed HIV infections (4). A wide range of comprehensive interventions has been adopted to resolve this challenge, with an emphasis on post-exposure prophylaxis (PEP) and pre-exposure prophylaxis (PrEP) (5, 6).

PEP is an evidence-based HIV prevention strategy in which a 28-day course of antiretroviral medication is administered to uninfected persons within 72 h (preferably within 24 h) after a recent possible exposure to HIV to minimize the risk of acquiring HIV. The effectiveness of the PEP in reducing HIV transmission has been reported in different studies (7, 8), and guidelines in different countries have been developed for PEP usage (9–12), including China (6). However, the overall uptake of PEP among MSM remains relatively low. Generally, only 4–6% of MSM who engaged in high-risk sexual behaviors (e.g., had unprotected anal intercourse with casual partners or substance use during anal sex in the past 6 months) reported having used PEP (13). Qualitative and quantitative studies reported multiple barriers to PEP uptake among MSM including low awareness of HIV infection risk, lack of PEP accessibility, and concerns about sexual risk compensation after PEP usage (14–16). Stigma against homosexuality and PEP usage further inhibits the effective delivery of PEP services for MSM (17). Therefore, innovative and effective approaches are needed to support PEP implementation in MSM.

Nearly universal mobile phone ownership provides MSM an opportunity to move away from traditional ways of meeting partners, such as bars, to seeking sexual partners through geosocial networking applications, and instant messaging apps. Integrated online-to-offline (O2O) models for HIV prevention are feasible and acceptable among MSM due to their help in identifying and engaging key populations, and seamlessly transitioning from online to offline services. O2O models in HIV service practice refer to the linkage between online service utilization and subsequent offline clinical service uptake and had been adopted in promoting the uptake of PrEP usage and HIV testing among MSM (18, 19). To date, China has relied heavily on traditional offline outreach models for PEP scale-up, despite the inherent challenges of engaging hard-to-reach MSM (20). This gap identifies a need for exploring O2O model implementation to promote PEP uptake in MSM.

Our study proposes to design and evaluate an O2O-based delivery model for HIV PEP uptake in Chinese MSM (O2O-PEP). The O2O-PEP model mainly comprises four components: a gamification-based PEP education package, an online HIV infection risk assessment tool, a free online booking system, and offline PEP prescription and related health services. We hypothesize that this O2O-PEP model could successfully bridge online outreach and offline PEP uptake and promote PEP uptake and continuation in MSM.

## Methods and materials

### The theoretical foundation for the O2O-PEP delivery model

Figure 1 displays the study's conceptual framework. The O2O-PEP model is developed following the Levesque framework (21), which conceptualizes five dimensions of accessibility of health services: approachability, acceptability, availability, affordability, and appropriateness, with five corresponding abilities attributed to health users: the ability to perceive, ability to seek, ability to reach, ability to pay, and ability to engage. The Levesque framework has been widely used in intervention studies, including promoting HIV testing and PrEP usage (22).

**Figure 1 F1:**
[figure not shown]
The conceptual framework for the postexposure prophylaxis (PEP) uptake intervention. The conceptual framework in our study is informed by the Levesque framework, including five domains of accessibility of health services: approachability, acceptability, availability, affordability, and appropriateness.

### Development of the O2O-PEP model

We followed the recommendations by Anand et al. (23) to design an integrated O2O model. The overview of the model construction is presented in Figure 2 and contains the following four steps:

**Figure 2 F2:**
[figure not shown]
Overview of O2O-PEP model. O2O, Online to Offline, PEP, Post-Exposure Prophylaxis.

#### Step 1. Establishing an integrated interdisciplinary team

Our interdisciplinary team consists of an online service team, an offline service team, and a technology team. The online service team includes HIV researchers and community-based organization (CBO) working staff, whose main task is to develop online PEP healthcare education packages and provide e-counseling support when needed. A doctor and a nurse in a hospital specializing in HIV management compose the offline service team, whose main task is to start a PEP regimen (the doctor) and PEP counseling for MSM (the nurse). The O2O-PEP model will be developed with VeiRui Technology (Beijing, China), a firm specializing in developing gamification-based software. The authors ([name], [name], and [name]) will be directly involved in creating requirements for the model.

#### Step 2. The first round of focus group discussions among Chinese MSM and healthcare providers

This step contains several FGDs with different populations before the model development: (1) MSM living in Qingdao, Beijing, and Jiangsu, China; (2) HIV-related service providers in CBOs; and (3) clinical health workers who are working in public health centers for HIV management (e.g., hospitals and centers for disease prevention and control). FGDs cover the following topics: HIV and PEP knowledge (only for MSM); current use of and access to WeChat and other mini-app technologies, and their potential role in promoting HIV prevention; opinions about the components of the model and what other functions should be included in this model; whether the model would be used after the construction; and how the model should be incorporated into routine HIV service sessions (only for healthcare providers). Online and offline in-person FGDs are both adopted; online FGDs use the cloud-based Tencent meeting, which provides an easy-to-use video conference that enables users to host or join meetings anytime anywhere. Each FGD lasts ~1 h and is conducted by 3 trained facilitators who are familiar with the study goals.

#### Step 3. Building version 1.0 of the O2O-PEP model

During this period, we partner with VeiRui Technology to build version 1.0 of the O2O-PEP model. Preliminary data from step 2 will be analyzed to build the model and applied through the WeChat mini-app. WeChat is an instant messaging and social media app developed by Tencent (Tencent Holdings Ltd., China), and it has been widely used in chronic disease management and HIV interventions (24, 25). The WeChat mini-app is an app built within the WeChat platform, which provides its users with an all-in-one experience. The O2O-PEP model initially consists of the following four main components.

#### An online HIV infection risk assessment tool

To identify assessment questions that could be used for recommending PEP usage, we will first review existing HIV infection risk assessment tools or variables positively associated with HIV infection, and then search PEP usage-related guidelines in different countries. The final assessment questions would include the time lag between sexual exposure and initial assessment (<72 h), and variables related to sexual exposures and sexual partners. According to users' responses to this tool, they will be divided into two groups: high risk of HIV infection vs. low risk of HIV infection.

#### Gamification-based education package for PEP

Gamification is a simulation technology using game design elements (e.g., challenges, points, and rewards) in non-game contexts. Advantages of gamification include (1) no time- and location-boundedness, as it provides low-risk learning, (2) less resource requirement as it offers contactless learning without a teacher, and (3) users' increased level of focus and attention as the unpredictability is embedded within the simulation (26, 27). Some studies have adopted gamification design in HIV interventions, such as reducing shame levels and risky sexual behaviors in MSM and increasing self-efficacy for HIV status disclosure in HIV-positive MSM (28, 29). The specific goals of the gamification-based education package for PEP in our study include (1) improving awareness and self-efficacy of PEP uptake, and (2) helping MSM understand the potential consequences of complying with or discontinuing PEP usage. When users involve in this gamification, they are always in situations where they must make decisions about PEP usage and corresponding consequences based on their choice, for instance, using or not using PEP, compliance with or discontinuation of PEP follow-up. Users' curiosity about “what will happen when they make different choices” is key to user engagement in the module. They are also exposed to valuable learning materials such as PEP usage timelines, laboratory testing, and caveats for PEP usage.

#### Free online booking system

Participants can click on the booking system link on the screen at any time during their immersion in the gamification to make online bookings anonymously and schedule appointments for their offline clinic visits. If participants schedule successfully, they will receive an auto-generated text message confirming the booking summary, which includes an e-ticket with booking details, a map to the clinic site, and a quick response (QR) code. The code is later scanned by the clinical service provider using a mobile app at check-in.

#### Offline PEP prescription and related health services

When MSM transfer from online to offline health services, healthcare providers should first confirm the participants' identity by scanning the QR code generated by online bookings for MSM. Then the doctor in the hospital starts the PEP regimen following the national PEP guideline (6), which includes laboratory testing and PEP prescription. The nurse in the same hospital is mainly responsible for PEP-related counseling, such as acute HIV infection symptoms, PEP-related side effects, risky behavior reduction, and PEP follow-ups.

#### Step 4. The second round of FGDs for model refinement and external usability test

After completion of version 1.0 of the O2O-PEP model, we will further conduct FGDs with MSM and healthcare workers who will be sent to the preliminary model to test the model and solicit opinions on the functionality of the mini-app. Glitches internal to the O2O-PEP model will be remedied during this period, including issues with log-ins, navigation, functionality, and para-data collection. These FGDs will be conducted by the same three facilitators in step 2.

After developing a polished version of the O2O-PEP model, we will conduct a 1-week, single-arm, pilot study among ten MSM aged 18 years or older to assess whether users could successfully navigate the model. MSM who participated in previous FGDs are encouraged to participate in this pilot test, as their feedback will provide useful insights to the research team. Upon completion of the pilot test, all participants will complete an online individual in-depth interview with study staff to provide feedback on functionality, bugs encountered, potential safety concerns, and experiences using the model. These ten participants would also complete the System Usability Scale (SUS) testing for the model usability assessment (30). SUS is a ten-item Likert Scale (0–10) giving an overall view of subjective assessment of the usability of a variety of products including websites and mobile phones, with a score <50 (out of 100) indicating the product is unacceptable, while if the score is more than 90, the product may be superior.

### Pilot randomized controlled trial

#### Study design and participants

The purpose of the pilot study is to assess the feasibility, acceptability, and preliminary evidence of the efficacy of the O2O-PEP model in increasing PEP uptake among MSM through a pilot two-arm stratified RCT comparing the O2O-PEP group with the standard care group (Figure 3). Participants will be recruited via online social media and offline CBOs. MSM are eligible to participate in our pilot study if they (1) are 18 years or older, (2) are assigned male at birth, (3) ever had anal intercourse with a man, 3) have HIV-uninfected by a laboratory rapid antibody test, (4) are going to reside in Jiangsu province and Qingdao city in the following 6 months after recruitment, (5) own a smartphone with Android-based operating system, (6) can access the WeChat app during the study period, and (7) are able and willing to provide electronic informed consent. Exclusion criteria include (1) self-reporting concomitant use of HIV PrEP at study entry, (2) creatinine clearance <30 ml/min, (3) known co-infection with chronic hepatitis B at enrollment, (4) participating in another research intervention related to PEP, (5) mental health disorders that may compromise adherence or safety, such as memory loss, cognition impairment, or communication disorders (assessed by an experienced clinical psychologist who is not involved in the study), and (6) presence of acute HIV infection symptoms [assessed by the Amsterdam score (31)].

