##### The intervention group (the O2O-PEP mini-app)

The O2O-PEP mini-app is the primary user-oriented platform for the intervention group. Following randomization, intervention group participants are directed to the gamification-based PEP education package, with a link to make online bookings anonymously available on the screen whenever participants want to click during the gamification procedure. After successful online booking, clients present their PEP prescription requisition e-ticket to the clinical doctor in the study-selected hospital, the clinical doctor will start the PEP regimen according to the Chinese national guideline, and the nurse in the same department will conduct essential PEP counseling when requested by participants. Participants will not be permitted to share the study advertisement with others. To restrict access to the min-app to intervention group participants only, those randomized into the intervention group will be provided a single-use verification code which will be entered to gain access to the intervention. Participants will have unlimited access to the mini-app after randomization until the end of the study.

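### The RCT's entry criteria do not bar men who already used the O2O-PEP app in phase 1, so app-exposed men could enter either arm

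*Protocol article*

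**What the plan says.** **Phase 1.** Step 2 holds focus groups with "MSM living in Qingdao, Beijing, and Jiangsu, China" before the app exists and asks for "opinions about the components of the model and what other functions should be included in this model". In Step 4, second-round focus group members receive version 1.0 "to test the model and solicit opinions on the functionality of the mini-app". A one-week "single-arm, pilot study among ten MSM aged 18 years or older" then uses the polished version, and all ten complete the SUS. On re-use of men, the protocol says that "MSM who participated in previous FGDs are encouraged to participate in this pilot test".

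**Phase 2.** Study settings describes a convenience sample from Jiangsu and Qingdao, recruited through two community organizations. Study design and participants gives six numbered exclusions. Only number (4), "participating in another research intervention related to PEP", comes near the point. The items listed for the web screener under Participant enrollment do not include phase 1 participation.

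**Protection of the contrast.** The intervention section sets up a single-use verification code "To restrict access to the min-app to intervention group participants only", and the control section says that controls are not sent to the app. Both measures start at randomization.

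**The concern.** The protocol treats access to the app by controls as something to prevent, but its safeguard starts too late to deal with use before randomization. Two primary outcomes are exposed.

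- **PEP initiation.** A control who has already worked through the education package has received part of what the trial sets out to contrast. PEP knowledge, a secondary outcome, is open to the same effect. The efficacy analysis is an unadjusted risk ratio and randomization is stratified by HIV risk only, so earlier exposure is neither balanced by design nor adjusted for.
- **Acceptability.** The SUS is a primary outcome in Table 1, with a score of 50 as the minimum. A phase 1 tester assigned to the app would be rating it on that scale for a second time and is not a new user.

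**Working it through.** **1. Who could pass through.** The phase 1 groups set against the RCT rules:

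| Phase 1 group | Used the app? | Location stated? | Barred from the RCT by phase 1 participation? |
|---|---|---|---|
| First-round focus groups (Step 2) | No, held before version 1.0 | Qingdao, Beijing, Jiangsu | No, but Beijing men would mostly fail the residence criterion |
| Second-round focus groups (Step 4) | Yes, version 1.0 | No | No |
| Ten usability testers (Step 4) | Yes, polished version for one week | No, but earlier focus group members are encouraged to join | No |

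The concern therefore applies to the second and third rows. A man in those rows must still meet every other RCT criterion: HIV-negative, Android phone, residence, no PrEP use, and so on.

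**2. The plan's own effect size.** Sample size assumes a 5% control rate and a 9-point difference. Intervention rate = 5% + 9% = 14%, and 14/5 = 2.8, which matches the stated relative risk. These are planning values for the main trial of about 400, used here only as a scale.

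**3. Chance that a phase 1 man reaches the control arm.** Let m phase 1 app users be among 50 men split 25:25. The documents do not give m. P(at least one in control) = 1 − C(50−m, 25)/C(50, 25).

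| m | P(at least one in control) | Expected number per arm |
|---|---|---|
| 1 | 0.50 | 0.5 |
| 2 | 0.76 | 1 |
| 5 | 0.97 | 2.5 |
| 10 | >0.999 | 5 |

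The ten testers equal 10/50 = 20% of the RCT places, so five pre-exposed controls is the number expected only if all ten enrol.

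**4. Dilution.** Assumption: pre-exposed controls initiate PEP at the full intervention rate of 14%. With a share c of controls pre-exposed, control rate = (1 − c) × 5% + c × 14%.

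| Pre-exposed controls | c | Control rate | Difference | Risk ratio | Expected control events of 25 |
|---|---|---|---|---|---|
| 0 | 0 | 5.0% | 9.0 points | 2.8 | 1.25 |
| 1 | 0.04 | 0.96 × 5% + 0.04 × 14% = 5.36% | 8.64 points | 2.6 | 1.34 |
| 5 | 0.20 | 0.80 × 5% + 0.20 × 14% = 6.8% | 7.2 points | 2.1 | 1.70 |

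The intervention arm would expect 25 × 14% = 3.5 events.

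**5. SUS.** Shift in the mean = share of repeat raters × their score difference. Assumption: they differ from new users by 5 to 20 points in either direction. With 1 of 25 raters the shift is 0.04 × 5 to 0.04 × 20 = 0.2 to 0.8 points. With 5 of 25 it is 0.20 × 5 to 0.20 × 20 = 1 to 4 points. The sign is not known.

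**The case against.** The strongest reply is that this is silence in a condensed article. No sentence says that phase 1 men will enter the RCT, the exclusion list is not stated to be exhaustive, and a fuller protocol may close the gap. That limits what can be said about how often it would happen. It does not remove the point: the article prints a criterion on involvement in other PEP research, its wording misses this case, and nothing elsewhere covers it.

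A reader might also infer more than the text supports:

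- **That phase 1 men are invited into the RCT.** The encouragement in Step 4 concerns the ten-man usability test, which is also called a pilot.
- **That any phase 1 man qualifies.** Phase 1 is not described as screening for HIV status, phone type, PrEP use or hepatitis B, so some would fail on other grounds.
- **That every phase 1 man has had the PEP education.** First-round focus group members never saw the app.
- **That controls lose the whole contrast.** The model also includes online booking linked to prescription, and a former tester assigned to control would be without app access for the six months of follow-up.
- **That SUS scores are inflated because testers rate an app rebuilt to their wishes.** No revision after the ten-man test is documented, and men asked to find faults could score lower.
- **That 20% contamination is expected.** It is an upper scenario for the testers. Focus group members cannot simply be added on top, because the protocol encourages them to be testers.

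The size is also modest. Even with five pre-exposed controls, the expected control count rises by less than half an event (1.70 − 1.25 = 0.45), and a shift of up to 4 SUS points changes the acceptability decision only if the mean lies close to 50.

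**Conclusion.** The gap in eligibility is real; how much it would matter is unknown. As written, the criteria and screener items do not keep out men who used the app in second-round focus groups or the usability test, and the access code cannot undo that exposure. The likely effect on PEP initiation and knowledge is dilution. The effect on the SUS could go either way.

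For initiation, the illustrated loss runs from about 0.4 points (9 − 8.64) with one pre-exposed control to 1.8 points (9 − 7.2) with five. It rests on the main trial's planning rates, on pre-exposed controls behaving like intervention men, and on a number of enrolling phase 1 men that the documents do not give. This is a cheap improvement of minor to moderate severity. It is worth making beforehand because prior phase 1 participation is not among the variables in Table 1, and with 25 men per arm it would be hard to correct for later.

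**What to change.** Extend exclusion (4) to prior participation in phase 1 of this study. At a minimum it should name the second-round focus groups and the usability test; barring any phase 1 activity is simpler to state and to check. Add one question to the web eligibility screener, asked before consent and randomization, and apply it equally to men introduced by community organization staff.

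The cost is one clause, one screener item and the loss of a few easily reached recruits. If those recruits are needed, the weaker alternative is to record phase 1 participation at baseline and also report PEP initiation and the SUS without these men. That leaves still fewer men in arms of 25.
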